### Outcome measures

The primary outcome is functional mobility at six months measured using the patient-/parent-reported GOAL questionnaire.^20^ The GOAL is validated specifically for use in ambulant CP and is internationally accepted as the appropriate functional outcome measure for lower limb interventions in this population.^20^ The GOAL questionnaire consists of 48 items grouped into seven domains – A: activities of daily living and independence; B: gait function and mobility; C: pain, discomfort, and fatigue; D: physical activities, sports, and recreation; E: gait pattern and appearance; F: use of braces and mobility aids; and G: body image and self-esteem. A total GOAL score will be calculated in line with the scoring manual, ranging from 0 to 100, with higher values indicating better outcomes.

We will use the child version of the GOAL whenever possible and the parent version one if not. The families will be asked to decide which version is most appropriate as part of the consent process, and their decision will be recorded on the baseline clinical assessment form to enable consistent use of the same version during follow-up.

Secondary outcomes (Table I) are:

Patient-/parent-reported outcomes at six and 12 months: independence measured using the GOAL subdomain A; balance measured using the GOAL subdomains A, B, D; pain and discomfort measured using the GOAL subdomain C;^20^ health-quality of life measured using the EQ-5D-Y;^23^ educational attendance record (number of days off school); exercise adherence; and additional physiotherapy treatment received outside of the trial.Clinician-assessed outcomes at six months: muscle strength measured using the Five Times Sit-to-Stand Test for adolescents with CP; and motor function using the Timed Up and Go test.^21,22^

The participants’ timeline through the trial is presented in Table II. A flowchart is presented in Figure 1.

### Patient and public involvement

Young people and their families have been involved in the development of this trial in a number of ways, including the format of the intervention and choice of primary outcome, and are representatives on the ROBUST Trial management group and trial steering group. We have also set up young person and parent advisory groups (YP/PAGs) to further support the trial and advise on the trial intervention materials, including the trial website, ROBUST Intervention app, participant and parent information sheets, and potential strategies to enhance recruitment and retention. In accordance with the Generation R advice (a network of young people supporting design of paediatric research in the UK),^34^ we will work with young people and parents on optimal ways to communicate the results of the trial to patients and the wider public.

### Adverse events

The potential occurrence of adverse events related to the intervention (Supplementary Material) will be recorded. The intervention has been designed to introduce a gradual increase in strength, thus minimizing the risk of musculoskeletal injury. Participants and their parent/guardian will be provided with information on the potential adverse events resulting from exercise as part of their treatment, including what they should do if they experience an adverse event, as would happen as part of standard NHS procedures. The participants and their parent/guardian will be asked to notify the treating therapist, as would occur during normal practice, if they suspect that they are suffering an adverse effect. In addition, at the six-month clinical follow-up visit, participants and their parent/guardian will be asked if they have experienced any adverse events. Expected general side effects of any form of exercise, such as delayed onset muscle soreness and temporary increases in pain (< seven days), will not be recorded as adverse events. Serious adverse events (SAEs) (defined as any unexpected medical occurrence that results in death, is life-threatening, requires hospitalization or prolongation of existing hospitalization, results in persistent or significant disability or incapacity, or is otherwise considered medically significant by the investigator) are very rare and are highly unlikely to occur as a result of the intervention delivered in this trial. However, if a SAE arises from the participant’s enrolment on the trial to their allocated intervention, standard procedures for recording and reporting SAEs will then apply.

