**Secondary outcomes**		
Muscle strength (clinician assessed)	Five Times Sit-to-Stand Test for adolescents with CP^21^	0, 6
Motor function (clinician assessed)	Timed Up and Go test^22^	0, 6
Independence	GOAL subdomain A^20^	0, 6, 12
Balance	GOAL subdomains A,B,D^20^	0, 6, 12
Pain and discomfort	GOAL subdomain C^20^	0, 6, 12
Health-related quality of life	EQ-5D-Y^23^	0, 6, 12
Educational outcomes	Educational attendance record (days)	0, 6, 12
Exercise adherence	Participant/Parent self-reported adherence	6, 12
Additional physiotherapy treatment	Participant/Parent self-reported treatment	6, 12

CP, cerebral palsy; EQ-5D-Y, youth version of the EuroQol five-dimension questionnaire.

**Table II. T2:** Participant timeline.

Timepoint (from randomization)	Pre-randomization	Baseline	0 to 4 mths	6-mth follow-up	12-mth follow-up

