### Interventions

Full details of the ROBUST trial interventions and their development will be published elsewhere in accordance with the TIDieR Statement;^29^ they are described here in brief.

Progressive resistance exercise programme: the participants randomized to the progressive resistance exercise programme will receive a 16-week individually tailored, structured exercise and advice programme, overseen by a physiotherapist, which consists of six one-to-one sessions. The 16-week training period allows time for the neurophysiological response to resistance training and for regular performance of exercises to become part of daily routine.^30^ The six physiotherapy-supervised sessions with the young person and the provision of parent/guardian training aim to initiate engagement in longer-term independent exercise. The first physiotherapy session will be up to 90 minutes, followed by five additional physiotherapy sessions of up to 60 minutes. The sessions will be offered at times that minimize disruption to education, consistent with NHS care for this patient group. Appointments will be coordinated so that participants typically start their first exercise session within two to four weeks of randomization, as per local appointment availability. Sessions will be in an outpatient setting or in the participants’ home or educational setting according to clinical need and local service provision. Participants will be advised to complete the exercise programme at home three times per week on non-consecutive days.

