Concomitant care: all participants will be advised to maintain their usual physiotherapy care, which may include the use of orthotics, and other forms of treatment during the trial (as long as this does not include a progressive resistance exercise programme), but will be informed that they should use the usual clinical referral routes to do so. We will record and monitor any additional physiotherapy received outside of the trial intervention and prescribed during the trial follow-up period.

Training and monitoring of intervention delivery, adherence, and fidelity: physiotherapists delivering the trial interventions will have access to a comprehensive intervention manual and will be required to have undertaken trial-specific training, delivered by a research physiotherapist. The physiotherapists will be experienced practitioners, under the supervision of one of the research physiotherapists (CB, HW) on the central trial team. The training will include comprehensive guidance on the theory and practical delivery of the trial interventions.

A rigorous quality control programme will be conducted to ensure protocol and intervention fidelity (i.e. the exercises being undertaken according to the protocol). Quality assurance checks will be made by the trial team, who will observe treatment sessions by physiotherapists. Site visits will be conducted periodically (minimum one visit per site per year) to observe the recruitment, consent, and randomization procedures, data collection, follow-up assessments, intervention, and usual care session(s).

We will also monitor adherence to treatment (participants undertaking the prescribed number of sessions and exercises), by logging aspects of the intervention. This will include the name of the exercises prescribed, the duration of physiotherapy appointments attended (and any additional contact), the number of sessions per week undertaken at home without physiotherapy supervision, and whether the session was completed, partially completed, or not completed. Treatment logs will be maintained on the REDCap trial website by the trial physiotherapists. At six and 12 months of follow-up, we will also record longer-term self-reported adherence.

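### Short pain that stops the programme, leads to health care or keeps recurring can go unrecorded as an adverse event, and it occurs before the first follow-up pain score

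*Protocol article*

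**What the plan says.** All references are to the protocol article.

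- **Adverse events.** Adverse events related to the intervention are to be recorded. Families are asked to tell the treating therapist about suspected adverse effects, and are asked again at the six-month clinic visit. One sentence leaves out the effects that any exercise can be expected to have; it reads in part: "such as delayed onset muscle soreness and temporary increases in pain (< seven days), will not be recorded as adverse events". A separate standard procedure covers events that are serious.
- **Interventions, schedule.** Those in the intervention arm "will receive a 16-week individually tailored, structured exercise and advice programme, overseen by a physiotherapist, which consists of six one-to-one sessions". The home frequency is stated separately: "Participants will be advised to complete the exercise programme at home three times per week on non-consecutive days". On timing, the aim for appointments is given as "participants typically start their first exercise session within two to four weeks of randomization".
- **Outcome measures and Table I.** The secondary outcomes include "pain and discomfort measured using the GOAL subdomain C", scored at 0, 6 and 12 months. Under Follow-up data collection, the six and 12 months are counted from randomization.
- **Interventions, training and monitoring.** For unsupervised home sessions the adherence log notes "whether the session was completed, partially completed, or not completed". No reason for non-completion is among the listed items.

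**The concern.** The exclusion has a duration limit but no exception based on consequence. A participant whose pain leads to stopping the programme, and then settles within a week of stopping, can be read as having an expected, temporary increase in pain. So can one who sees a health professional about a three-day flare. The text also does not say whether repeated short flares count as one episode or as several, each under the limit.

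The section itself names soreness and temporary pain as expected effects of exercise, and the Introduction lists pain among the consequences of CP. If short, treatment-limiting pain is neither logged as an event nor present at the time of the pain score, the tolerability comparison will understate it. The understatement would fall mainly on the arm that is prescribed the resistance programme. The data safety and monitoring committee would not see these episodes as adverse events.

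There is also a consequence for adherence. The Statistical analysis section defines adherence as all six physiotherapy sessions but lets the therapist declare treatment complete in fewer. Without a recorded reason, stopping because of pain cannot be told apart from other non-adherence.

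**Working it through.** The plan states no figure on this point that could be reproduced. The check is calendar arithmetic, followed by a comparison of the recording routes.

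**Inputs.** Start 2 to 4 weeks after randomization, programme length 16 weeks and home exercise three times a week (Interventions); follow-up clock from randomization (Follow-up data collection); pain score at 0, 6 and 12 months (Table I).

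**Spacing of sessions.**
- Number advised: 16 × 3 = 48 home sessions.
- Mean spacing: 7 / 3 = 2.33 days. On non-consecutive days the gaps are two or three days.
- A flare that settles before the next session therefore lasts less than seven days, however many sessions it follows.

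**Distance from programme end to the next pain score.**
- Typical end: 2 + 16 = week 18 to 4 + 16 = week 20.
- Six months: 365.25 / 2 / 7 = 26.1 weeks.
- Gap: 26.1 − 20 = 6.1 weeks to 26.1 − 18 = 8.1 weeks.
- If the end is taken instead from the 0 to 4 month column of Table II: 365.25 / 3 / 7 = 17.4 weeks, and 26.1 − 17.4 = 8.7 weeks.

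**Can another stated route catch short pain during the programme?**

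| Route | What it catches | Short pain that limits treatment or recurs |
|---|---|---|
| Telling the treating therapist | Suspected adverse effects | Can be reported, but the same exclusion decides whether it is recorded |
| Question at the six-month visit | Adverse events, with no restriction by arm | Same exclusion applies |
| Serious adverse event procedure | Unexpected events meeting a seriousness criterion, including medical significance in the investigator's judgement | Pain already classed as expected does not clearly qualify |
| GOAL subdomain C | Pain at 0, 6 and 12 months | No score during the 16 weeks; the article gives no recall period |
| Adherence log | Completion status of home sessions | No reason listed |
| Exercise diaries | Shared between participant and physiotherapist, reviewed at each session | Not described as trial data or as recording pain |

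No route in the article clearly records it.

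**The case against.** The strongest reply is that the exclusion is narrower than its examples suggest. The sentence opens by limiting it to side effects that are expected and general to any exercise. Pain that makes an adolescent give up the programme or seek care is arguably not that, and a sensible therapist might record it. This has force, but the article leaves the decision to each therapist's reading and does not state the exception.

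A second reply is that this is a condensed article: the supplementary adverse event material is not shown, and the log items are introduced as inclusions rather than as a complete list. A fuller document may already hold the exception or a reason field. That stands as a caveat. The point nevertheless concerns a rule that the article states, not a detail it leaves out.

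Third, leaving ordinary exercise soreness out of adverse event recording is a legitimate and openly declared choice. That stands in full. Recording every recurrent flare as an adverse event would be a debatable trade-off.

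A reader might go further and infer that pain caused by the programme is captured nowhere. The documents do not support this. Pain lasting seven days or more remains recordable, serious adverse events have their own procedure, and persistent pain can show in GOAL subdomain C at six and 12 months. Longer-term independent exercise is an aim, so some participants may still be exercising when they complete the six-month score.

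A reader might also work out that a two-day flare after every session gives 48 × 2 = 96 pain-days out of 16 × 7 = 112 with no recorded event. That is hypothetical. The article gives no flare duration, and the sum assumes that every advised session is done.

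**Conclusion.** The point holds in a limited form. Short pain during the 16 weeks that stops the programme, leads to health care or keeps recurring can go unrecorded as an adverse event, and the next pain score comes about 6 to 8 weeks after the programme typically ends. How often this would happen cannot be estimated from the article.

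The conclusion assumes typical timing (start at week 2 to 4, full 16 weeks), that therapists apply the exclusion as it is worded, and that the unseen supplementary material adds no exception. The severity is minor to moderate: the completeness of the harm reporting is affected, while the primary outcome, its analysis and the sample size are not.

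**What to change.** The changes concern recording only and leave clinical management as it is.

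1. Keep the exclusion for ordinary soreness, and add one sentence: pain of any duration is recorded as an adverse event when it leads to the programme being stopped or to contact with a health professional.
2. Add a reason (pain or other) to the existing session-completion field in the log. This makes recurrent pain visible without turning each flare into an adverse event.
3. Word the existing six-month adverse event question so that, in both arms, it covers such pain since randomization.

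If the full protocol or the supplementary material already contains these provisions, a line in the Adverse events section pointing to them is enough.

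The cost is one sentence, one log field and a rewording of a question already asked, plus a few more minor events to process. It is best done early, because data on pain during the programme cannot be reliably recovered afterwards.

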### Blinding

Participants will be informed of their treatment group by the research facilitator at the initial appointment. Participants will not be blinded to the treatment allocation, nor will the physiotherapists delivering the intervention. The trial statistician and data entry personnel will also not be blinded to the treatment allocation. Physiotherapists performing the six-month follow-up outcome assessment will be blinded to treatment allocation, where possible provided that staffing levels allow, as will the remaining members of the central trial management team until after the data analysis is complete.

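### The SAE definition admits only unexpected events, so a serious event judged expected is, read literally, not an SAE

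*Protocol article*

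**What the plan says.** All the safety rules shown are in the protocol article, Methods, Adverse events.

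- **SAE definition.** SAEs are "defined as any unexpected medical occurrence that results in death, is life-threatening, requires hospitalization or prolongation of existing hospitalization", and the list continues with lasting disability and events the investigator considers medically significant.
- **SAE reporting.** "if a SAE arises from the participant’s enrolment on the trial to their allocated intervention, standard procedures for recording and reporting SAEs will then apply".
- **AE scope.** "The potential occurrence of adverse events related to the intervention (Supplementary Material) will be recorded".
- **AE exclusion.** Expected general effects of exercise are left out. Muscle soreness is one example, and the sentence ends: "temporary increases in pain (< seven days), will not be recorded as adverse events".
- **AE route 1, spontaneous.** Participants and parents "will be asked to notify the treating therapist, as would occur during normal practice, if they suspect that they are suffering an adverse effect".
- **AE route 2, direct question.** "at the six-month clinical follow-up visit, participants and their parent/guardian will be asked if they have experienced any adverse events". No distinction is made between arms.

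Under Interventions, the exercise arm has six individual trial physiotherapy sessions over 16 weeks. The usual-care arm has one trial session, on top of routine appointments whose number is not given. Under Ethics and dissemination, an independent data safety and monitoring committee reviews safety data.

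**The concern.** Seriousness describes the outcome of an event: death, threat to life, admission, disability. Expectedness describes whether the event was foreseen. They are separate judgements, and the usual definition of an SAE says *untoward* and leaves expectedness to a later step. Here the second judgement decides whether the first is made at all.

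The harms most plausibly caused by an exercise programme are also the foreseeable ones. The same section names musculoskeletal injury as the risk that the gradual progression is meant to minimise. If an injury of that kind led to admission and someone judged it expected, the wording would exclude it from the SAE count. The committee can review only what the recording rules pass to it.

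The secondary matter is ascertainment. One of the two AE routes runs through a therapist whom the trial schedules more often in one arm than in the other.

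**Working it through.** The plan gives no figure on this point, so there is none to reproduce, and the sample size is unaffected.

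**Step 1: apply the SAE text literally.** Take an event that meets a seriousness criterion and classify it by expectedness and relatedness.

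| Serious event | Meets the SAE definition? | Do SAE procedures apply? |
|---|---|---|
| Unexpected, related | Yes | Yes if the reporting sentence is causal; if it is a time window, only inside it |
| Unexpected, unrelated | Yes | No if causal; if a time window, only inside it |
| Expected, related | No | No; at most an ordinary AE |
| Expected, unrelated | No | No; also outside the AE scope, which covers intervention-related events |

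Both expected rows drop out under either reading of the reporting sentence, so the defect lies in the definition. The second row shows why the reporting sentence also needs rewording: its two readings give different answers. As a time window it is odd too, since it runs from enrolment to the allocated intervention and sets no clear end date.

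**Step 2: can *unexpected* be read harmlessly?** It might mean only that planned admissions are excluded, but the text does not say so. In the same section, *expected* labels a class of effects that is not recorded, and that class is introduced by examples and not by a closed list. Nothing else in the article corrects the definition.

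**Step 3: how much could unequal contact matter?** The documents give no AE rates or reporting probabilities, so this is illustration only. Inputs:

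- 167 per arm (Sample size section).
- Trial sessions K = 6 against K = 1 (Interventions section).
- Assumed: true AE risk p = 10% in both arms.
- Assumed: chance r = 10% to 30% that an event is reported at each later trial session.
- Assumed: recall q at the six-month question.
- Assumed: events spread evenly over the programme, and routine appointments ignored.

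An event is followed by j = 0, 1, …, K − 1 trial sessions with equal chance. Capture through the therapist is a = (1/K) Σ [1 − (1 − r)^j]. Total capture is c = 1 − (1 − a)(1 − q). The expected count is 167 × p × c.

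- K = 6, r = 0.1: a = (0 + 0.1 + 0.19 + 0.271 + 0.3439 + 0.40951)/6 = 0.219.
- K = 6, r = 0.3: a = (0 + 0.3 + 0.51 + 0.657 + 0.7599 + 0.83193)/6 = 0.510.
- K = 1: a = 0, so usual care relies on the six-month question alone.

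True events per arm are 167 × 0.10 = 16.7.

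| Recall q | Exercise arm | Usual care |
|---|---|---|
| 0% | 3.7 to 8.5 | 0 |
| 50% | 10.2 to 12.6 | 16.7 × 0.5 = 8.35 |
| 80% | 14.1 to 15.1 | 16.7 × 0.8 = 13.4 |
| 100% | 16.7 | 16.7 |

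With p = 20% every entry doubles. The false excess falls on the exercise arm. It shrinks to about one or two events at 80% recall (14.1 − 13.4 = 0.7; 15.1 − 13.4 = 1.7) and vanishes with complete recall.

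**The case against.** **On the definition.** The section names only muscle soreness and short-lived pain as expected. It never says that an injury needing admission is expected, and it regards SAEs as highly unlikely. Standard SAE procedures and an independent committee are in place. This limits how often the wording would bite, and it means that no actual undercount has been shown. It does not repair the definition: standard procedures apply only to events that the definition admits, and who judges expectedness, and against what list, is not stated in the article.

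**On unequal contact.** The same direct question goes to both arms at six months, after the 16-week programme has ended. Families can notify without waiting for a session. Controls keep routine physiotherapy, although the article does not say whether those therapists report to the trial. AEs are not among the listed outcomes and no between-arm comparison of them is stated. All of this stands, so the point remains a risk.

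**Stronger readings that the article does not support:**

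- *No AEs are sought after month six.* The article describes no later question, but it points to Supplementary Material on adverse events that is not shown, and it condenses a fuller protocol. Silence here is not evidence.
- *About 67 participants (20% of 334) may never be asked.* The 20% is the sample-size allowance for loss to follow-up and not a clinic non-attendance rate. Under Follow-up data collection, non-attenders are telephoned and sent a new appointment.
- *Six sessions against one gives a ratio of detection.* The documents give no detection probability per session, the first session starts the programme and cannot reveal harm from it, and such a ratio stops before the question common to both arms.
- *The AE question unblinds the assessor.* The Blinding section says "Physiotherapists performing the six-month follow-up outcome assessment will be blinded to treatment allocation", qualified as where possible. The Adverse events section does not say who asks about AEs or whether this comes before or after the timed tests, so unblinding is conjecture.

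**Conclusion.** The SAE definition is wrong as worded and should be amended. It makes seriousness depend on expectedness, and on a literal reading every serious event judged expected falls outside SAE recording and would not reach the safety committee as an SAE. The number of events affected cannot be estimated from the article and is probably small. The reporting sentence is ambiguous between a time window and a causal condition, and the two differ for every unrelated serious event inside the window.

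Unequal ascertainment of non-serious events is a risk and not a demonstrated error. Its size depends on recall at six months. Under the assumptions shown it runs from no excess at full recall to about 2 to 4 events in the exercise arm at 50% recall (10.2 − 8.35 = 1.85; 12.6 − 8.35 = 4.25). A reader might infer that harms will be undercounted and counted unequally by arm; the article does not establish either.

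**What to change.** 1. In the SAE definition, replace *unexpected* with *untoward*. Record expectedness and relatedness as separate assessments made after seriousness.
2. Reword the reporting sentence so that it says plainly whether it sets a time window (with start and end) or a causal condition.
3. State that any between-arm AE comparison will use the six-month question put to both arms, with therapist-notified events reported separately by arm.

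The cost is a minor wording amendment and one extra line in the safety tables. There is no effect on sample size, visits or the primary analysis.
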